## Abstract

**Background:**

Chronic central serous chorioretinopathy (cCSC) is an eye disease characterized by an accumulation of serous fluid under the retina. It is postulated that this fluid accumulation results from hyperpermeability and swelling of the choroid, the underlying vascular tissue of the eye, causing a dysfunction of the retinal pigment epithelium. This fluid accumulation causes neuroretinal detachment. A prolonged neuroretinal detachment in the macula can lead to permanent vision loss. Therefore, treatment is aimed primarily at achieving resolution of subretinal fluid, preferably within the first 4 months after diagnosis of the disease. A broad spectrum of treatment modalities has been investigated in cCSC, but no consensus exists on the optimal treatment of cCSC. Currently, photodynamic therapy (PDT) and high-density subthreshold micropulse laser treatment (HSML) are among the most frequently cited treatments in obtaining successful neuroretinal reattachment.

**Methods/Design:**

This is a randomized, controlled, open-label, multicenter trial comparing the efficacy of half-dose PDT to HSML in treating patients with cCSC. A total of 156 patients will be recruited, 78 patients in each treatment arm, with a maximum follow-up duration of 8 months after the first treatment. A complete ophthalmological examination with vision-related quality of life (NEI VFQ-25) and stress questionnaires, will be performed at baseline, 6 to 8 weeks after the first treatment, 6 to 8 weeks after a second treatment (if necessary), and at the final follow-up visit at 7 to 8 months after the first treatment. Treatment visits will be scheduled within 3 weeks after the baseline visit, and within 3 weeks after the first control visit, if a second treatment is required.

**Discussion:**

Both half-dose PDT and HSML may be effective treatments in cCSC, but because of the lack of prospective randomized controlled trials, which treatment should be the first choice remains unclear. The aim of this study is to compare the efficacy of half-dose PDT to HSML. The primary endpoint to evaluate efficacy will be a complete absence of subretinal fluid on optical coherence tomography after treatment. Secondary functional endpoints include change in Early Treatment Diabetic Retinopathy Study (ETDRS) best-corrected visual acuity, retinal sensitivity on microperimetry, and NEI VFQ-25 questionnaire of visual functioning.

Registration number Institutional Review Board (CMO Arnhem-Nijmegen, the Netherlands): 2013/203 NL nr.: 41266.091.13

**Trial registration:**

ClinicalTrials.gov identifier: NCT01797861. Date of registration: 21 February 2013.

## Background

### Chronic central serous chorioretinopathy

Central serous chorioretinopathy (CSC) is a relatively common early-onset eye disease, characterized by an accumulation of leaked serous fluid under the retina, causing a detachment of the neuroretina. This subretinal fluid (SRF) leakage results from dysfunction of the retinal pigment epithelium (RPE), and the presence of choroidal congestion and thickening and hyperpermeability of the choroid implies an important role for choroidal abnormalities as an underlying cause for RPE dysfunction and SRF leakage in CSC [1–4].

Two main subtypes of CSC are generally distinguished: acute and chronic CSC (cCSC) [1–7]. Patients with acute CSC present with a sudden and marked central vision loss because of SRF leakage in the macula; this is due to a focal leak in the RPE that is visible on fluorescein angiography. Acute CSC generally has a favorable prognosis because the SRF often disappears spontaneously within 2 to 3 months, with either complete or almost complete recovery of vision. In contrast, cCSC is typically not self-limiting, and SRF persists for more than 3 months. Also, cCSC patients present at an older age, with a disease onset that is generally experienced as less sudden, and bilaterality in chronic CSC is common [8]. A history of acute CSC and/or an episode of acute vision loss compatible with acute CSC is present only rarely in chronic CSC patients [2, 8], which also points to a distinction between acute and chronic CSC. Patients with the cCSC phenotype have more diffuse multifocal leakage on fluorescein and indocyanine green (ICG) angiography, as well as irregularly distributed widespread RPE changes associated with varying degrees of more indistinct leakage on angiography (Fig. 1). Persistent serous neuroretinal detachments can cause progressive and irreversible photoreceptor damage, resulting in a poorer visual prognosis of cCSC as compared to acute CSC [2, 9, 10]. The etiology of CSC is largely unknown, but the use of corticosteroids is a risk factor, and possibly elevated cortisol levels, stress, “type A” personality, and pregnancy are also possible risk factors [1, 11–14]. The incidence of CSC is approximately six times higher in men than in women [1], although this male-to-female proportion seems to be less pronounced in cCSC and steroid-associated CSC. Recently, single-nucleotide polymorphisms in the *Complement Factor H* and *ARMS2* have been found to be associated with cCSC [15, 16].

**Fig. 1 Fig1:**
[figure not shown]
Multimodal imaging in chronic central serous chorioretinopathy. Examples of fluorescein angiography (FA), indocyanine green (ICG) angiography and spectral-domain optical coherence tomography (SD-OCT) in chronic central serous chorioretinopathy (cCSC). (**a-c**) Right eye of a patient with cCSC with more widespread leakage on FA (**a**) corresponding with hyperfluorescent areas on ICG angiography (**b**) and SRF on SD-OCT (**c**)

A prolonged neuroretinal detachment in the macula leads to progressive and permanent central visual loss due to photoreceptor atrophy. In addition, Piccolino et al. described the occurrence of not only SRF, but also of intraretinal fluid accumulations, posterior cystoid degeneration, and prolonged neuroretinal detachments in severe cCSC cases [17]. Nicolo et al. have shown that this posterior cystoid degeneration is associated with a poorer response to photodynamic therapy (PDT) [17, 18]. A loss of visual acuity with image distortion and a loss of color and contrast vision may have a significant impact on a patient’s personal and professional life. Early diagnosis and treatment is important to try to improve the visual outcome and quality of life, as long-term follow-up studies have shown that the natural course of cCSC often results in permanent visual loss [3, 9, 10, 19–25]. Therefore, several treatment options have emerged in an attempt to accelerate the resolution of SRF accumulation and to improve the visual outcome in patients with cCSC. Treatment within 4 months after the onset of the disease has been advocated by several authors, based on the observation that permanent visual loss may result from prolonged duration of disease [2, 3]. Photoreceptor atrophy in the fovea may occur, even after successful reattachment of the retina, after a duration of symptoms of approximately 4 months [9]. To date there is no international consensus on the optimal treatment protocol of cCSC.

### Photodynamic therapy in chronic central serous chorioretinopathy

A number of retrospective studies suggests that in 70 to 100 % of CSC patients, treatment with PDT, using the photosensitizing drug verteporfin (Visudyne™), is effective in reducing SRF, with an improvement of retinal anatomy, visual acuity [18, 26–30], and retinal sensitivity [31–35]. PDT treatment was developed originally as treatment for neovascular age-related macular degeneration, on which there are extensive data available [36, 37]. There are several other retinal diseases for which PDT with verteporfin is successfully used as an off-label treatment, such as choroidal hemangioma and polypoidal choroidal vasculopathy [37].

PDT with Visudyne™ (verteporfin for injection) is a two-stage procedure that first requires the intravenous administration of verteporfin, followed by the administration of non-thermal red light into the affected eye. Verteporfin is transported in the plasma primarily by lipoproteins. Once verteporfin is activated by light in the presence of oxygen, highly reactive, short-lived singlet oxygen and reactive oxygen radicals are generated. Verteporfin appears to accumulate preferentially in abnormal neovascularization (which is not present in cCSC) but also in the choroidal vasculature. The latter mechanism is of special interest in the treatment of cCSC because CSC primarily affects the choroidal circulation, resulting in multifocal areas of choroidal vascular hyperpermeability that may finally result in the accumulation of SRF. The therapeutic effect of PDT in cCSC is thought to result from short-term choriocapillaris hypoperfusion and long-term choroidal vascular remodeling, leading to reduction in choroidal congestion, vascular hyperpermeability, and extravascular leakage [38–40].

As mentioned previously, there is no international consensus on the optimal treatment protocol of cCSC. Nevertheless, PDT has emerged as the treatment of choice in many centers worldwide, based on the high rate of anatomic success, the increase of visual acuity, improvement in retinal sensitivity, and an excellent safety profile reported in many retrospective studies [3, 41–43]. The PDT strategies that are generally used are either with half the dose of verteporfin and full fluency (energy) of laser treatment, half the fluency level and the full dose of verteporfin, or half the treatment time using the full dose of verteporfin and full fluency, as compared to the original protocol that was used for neovascular age-related macular degeneration. These PDT strategies that use either half-dose of half-fluency treatment have been developed because a combination of the dosage and fluency that was originally used for the treatment of neovascular age-related macular degeneration showed a potentially higher risk of developing choroidal ischemia and retinal atrophic changes [36, 44–46]. The half-dose or half-fluency PDT strategies, however, have been shown to be safe and effective in relatively large retrospective studies and in one noncontrolled, nonrandomized prospective study by Chan et al. in cCSC patients with sufficient follow-up periods [3, 27, 29, 41].

Therefore, tailoring the therapy to obtain the maximal treatment effect with minimal toxicity is essential in treating patients with CSC. By reducing the dose of verteporfin, studies have demonstrated that the potential retinal damage caused by PDT can be minimized while the photodynamic effects in inducing choroidal vasculature changes required for treating CSC remain sufficient [2, 3, 18, 26–30, 41, 47]. None of the patients treated with this half-dose PDT protocol experienced any systemic adverse event (AE) associated with verteporfin infusion [27]. In several relatively large retrospective studies on half-dose PDT in CSC, none of the patients had any subjective or objective drop in vision immediately after PDT or at subsequent follow-up visits [18, 26–30]. This “safety-enhanced” protocol with half-dose verteporfin appeared to be one of the safest and effective treatment options in patients with active cCSC [23, 41]. In conclusion, a relatively large body of well-documented retrospective studies indicates that half-dose PDT is able to yield positive functional and anatomic outcomes while at the same time reducing the potential AEs associated with conventional PDT with full-dose verteporfin.

### High-density subthreshold micropulse laser therapy as an alternative treatment in chronic central serous chorioretinopathy

There are several retrospective studies that indicate that high-density subthreshold micropulse laser (HSML) therapy may be effective in 41 to 58 % of CSC patients [18, 48]. HSML treatment using a 810 nm wavelength is an established treatment option for a broad range of retinal diseases [49]. In this treatment, no photosensitizing drug is needed. This relatively new laser treatment modality may prevent damage to the neural retina that occurs in conventional (non-PDT) laser techniques by raising the temperature of the RPE below the protein-denaturation-threshold so that the thermal wave that reaches the neural retina is insufficient to cause either damage or a clinically visible end-point (opacified retina). It is different from subthreshold continuous wave in that more energy can be delivered to the RPE without neuroretinal damage using multiple short pulses. In contrast, in the continuous wave mode of conventional laser therapy, the laser energy is delivered with a single pulse with a duration of exposure of 0.1 to 0.5 s, most of the energy is absorbed by the RPE and the heat energy is transferred to the neurosensory retina leading to transient retinal swelling (visible end-point). As a result, conventional laser application in the macula may cause damage to the neuroretina and RPE, leading to central scotomas and possibly loss of visual acuity. Previous studies have shown that conventional laser treatment in CSC, in contrast to HSML treatment and half-dose PDT treatment, does not improve visual acuity, may cause photoreceptor damage, and may induce choroidal neovascularization [3]. Recently, studies using a relatively new 577 nm wavelength micropulse laser in subthreshold mode have also shown possible efficacy in the treatment of cCSC [50, 51].

### Outline of proposed clinical trial

The PLACE study is a superiority study because retrospective studies suggest that the rate of anatomical and functional success of PDT treatment might be higher than the success of HSML treatment. Therefore, a half-dose PDT treatment arm is challenged against a treatment arm of HSML treatment.

In this study, we want to define treatment success not only on the basis of structural parameters (anatomic success, for example, the absence of SRF after treatment), but also based on functional vision-related endpoints, which are most important from a patient’s perspective. These functional vision-related endpoints will include best-corrected visual acuity (BCVA), retinal sensitivity on microperimetry and score on a validated visual function questionnaire (the NEI-VFQ-25 questionnaire) http://www.psy.cmu.edu/~scohen/ [52].

With the results of this study, we hope to establish a strong scientific foundation for further research on the optimal treatment of patients with cCSC to improve the visual outcome and quality of life of this relatively frequently occurring eye disease.

### Objectives

#### Primary objective

The primary objective of this study is to investigate whether treatment of cCSC patients with macular SRF on optical coherence tomography (OCT) with half-dose PDT results in more eyes with an absence of SRF on the OCT as compared to HSML treatment.

#### Secondary objectives

The secondary objectives are to investigate the clinical outcome comparing half-dose PDT treatment with HSML treatment in patients with SRF due to active leakage in cCSC, based on evaluation of BCVA; the retinal sensitivity on microperimetry; and the subjective success score on the NEI-VFQ-25 questionnaire.

## Methods/Design

### Summary of trial design

This study is a multicenter, prospective, randomized, controlled, open-label study that will compare the efficacy and safety of two treatments in patients with cCSC. The first group of patients will receive half-dose PDT treatment. The second group of patients will receive 810 nm HSML treatment. Each patient will receive at least one treatment but may be eligible to receive a second treatment during follow-up (Fig. 2), which will be the same type of treatment as the first treatment: either half-dose PDT treatment or HSML treatment.

**Fig. 2 Fig2:**
[figure not shown]
Study flow chart

Potential eligible patients will be identified in one of five specialist ophthalmology trial sites, each led by one of the principal investigators (PIs).

Fundus photographs, fluorescein angiograms, ICG angiograms and OCT images collected at the screening visit will be sent to a central reading center (CRC). The CRC will review these images to confirm subject eligibility based on the characteristics specified in the inclusion and exclusion criteria. Once eligibility has been confirmed by the CRC, all other inclusion and exclusion criteria have been met at the baseline visit, and informed consent has been obtained, patients will be enrolled in the trial.

There are nine examinations that will be performed at the baseline assessment, 6 to 8 weeks after treatment (at evaluation visit 1, and if a second treatment is required, at evaluation visit 2), and at the final visit (7 to 8 months after start of the treatment). The six *anatomical* assessments include ophthalmoscopy, fundus photography, OCT, autofluorescence imaging, fluorescein angiography, and ICG angiography. The three *functional* assessments include visual acuity measurement, microperimetry, and a questionnaire on vision-related functioning.

Enrolled patients will be randomized at a 1:1 ratio to receive either half-dose PDT treatment or HSML treatment.

The total number of visits per patient is five (in case of one required treatment) or seven (in case of two required treatments). The duration of participant participation within the study is 7 to 8 months (Fig. 2).

An overview of the assessments in the trial are as follows:OphthalmoscopyThis examination will be performed by one of the ophthalmologists to confirm the diagnosis. The pupils will have to be dilated with 1.0 % tropicamide and 2.5 % phenylephrine for ophthalmoscopy to be performed.Fundus photographyThe fundus photography will be taken with a Topcon TRC-50 series fundus camera. The photographs will be taken with a 50°-field centered on the area of the macula.Optical coherence tomography (OCT) imagingPatients will be examined by noninvasive OCT imaging. OCT shows the different layers of the retina and is the imaging modality of choice to visualize subretinal and intraretinal fluid, for instance in cCSC. This examination is performed during mydriasis (dilated pupils). OCT imaging will be carried out with a Spectralis HRA + OCT (Heidelberg Engineering, Heidelberg, Germany).Fundus autofluorescence imagingFundus autofluorescence is a noninvasive imaging technique that is able to register changes of autofluorescence intensity in the retina, for instance due to accumulation of lipofuscin in the RPE. Fundus autofluorescence imaging will be carried out with a Spectralis HRA + OCT (Heidelberg Engineering, Heidelberg, Germany).Fluorescein and indocyanine green (ICG) angiographyTo perform fluorescein and ICG angiography, intravenous injection of fluorescein and ICG is required. During the angiography procedure, both (fluorescein and ICG) dyes may be injected at the same time or separately. Fluorescein reveals the retinal vasculature and may show areas of fluid leakage through the RPE, whereas the ICG dye images the choroidal vasculature. The visualization of both the retinal vasculature and RPE permeability (by fluorescein angiography) and choroidal vasculature (by ICG angiography) is essential to image the areas of abnormal anatomy and leakage that may guide treatment. Images of the study eye are taken at set times: 0 to 1 minute (several images covering the arterial and venous filling phases), 3 minutes, 6 minutes, 10 minutes, 15 minutes, and 20 minutes. Images of the nonstudy eye will be taken at 1 minute, 6 minutes, and 20 minutes. All images will be acquired with Spectralis HRA + OCT (Heidelberg Engineering, Heidelberg, Germany).Best-corrected visual acuity (BCVA)BCVA will be assessed for both eyes at all evaluation visits. To measure BCVA, early treatment diabetic retinopathy study (ETDRS) visual acuity testing charts will be used at a distance of 4 meters.MicroperimetryAll patients will be examined by noninvasive microperimetry. This technique is able to measure retinal sensitivity to light, and follow-up pre- and post-treatment changes in retinal sensitivity at predetermined loci in the macula. By using a reliable eye tracking system, this microperimetry system is able to exactly locate the areas of retina that have been tested previously, in order to ensure testing of identically the same area at follow-up. Microperimetry according to a standard protocol takes 5 to 8 minutes for each eye and will be performed with non-dilated pupils.QuestionnairesEach participant will be asked to complete a quality-of-life questionnaire based on the National Eye Institute Visual Function Questionnaire (NEI-VFQ-25) [52], and the Cohen Stress Questionnaire [53] [http://www.centervue.com/product.php?id=639]. NEI-VFQ-25 is a reliable and validated 25-item version of the 51-item National Eye Institute Visual Function Questionnaire [54]. The questionnaire is especially useful in settings such as clinical trials, where interview length is an important consideration. The Cohen Stress Questionnaire is a validated questionnaire indicating the stress level patients have been exposed to during the month before disease onset.

There will be standard operating procedures (SOPs) available to all investigators involved in the trial as well as in the trial master file for each of the described examinations.

### Primary and secondary endpoints

#### Primary endpoint

The primary endpoint of this study is to assess if there is a difference between the efficacy of half-dose PDT treatment versus the HSML treatment in patients with cCSC. The assessment of this efficacy will be based on the anatomical effect on OCT: absence of SRF versus persistent SRF, 6 to 8 weeks after treatment. After all, the absence or presence of fluid under the retina on the OCT scan is a direct reflection of the activity of the disease in these patients.

#### Secondary endpoints

For secondary endpoints, we will mainly look at three parameters that reflect the patient’s vision-related functioning. These three parameters are a standardized measurement of BCVA according to the ETDRS standards, a standardized measurement of sensitivity of the macula with microperimetry, and a standardized assessment of the patient’s vision-related quality of life using a validated questionnaire, the NEI-VFQ-25.

The secondary endpoints that will be assessed as a reflection of functional improvement after treatment include the following:Number of second treatments needed in each treatment arm.Mean change from baseline in ETDRS BCVA in the study eye at 6 to 8 weeks after treatment visit 1 and at 7 to 8 months after treatment visit 1, among the two treatment modalities.Mean change from evaluation visit 1 in ETDRS BCVA in the study eye at final evaluation (7 to 8 months after treatment visit 1), among those who required one treatment and those who required a second treatment, and among the two treatment modalities overall.Mean change from baseline in retinal sensitivity on microperimetry in the study eye at 6 to 8 weeks after treatment visit 1 and at 7 to 8 months after treatment visit 1 among the two treatment modalities.Mean change from baseline in the NEI-VFQ-25 questionnaire at 6 to 8 weeks after treatment visit 1 and at 7 to 8 months after treatment visit 1 among the two treatment modalities.An absence of SRF on evaluation with OCT scanning as compared to HSML treatment at 7 to 8 months follow-up after successful treatment (after treatment visit 1; “success” defined as an absence of SRF on OCT at 6 to 8 weeks after treatment).

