#### Retreatment criteria and considerations

At evaluation visit 1, at 6 to 8 weeks after treatment, an OCT scan of the retina will be performed, among other imaging examinations. If there still is SRF present in the macular area, a second treatment will be performed according to the protocol within 3 weeks after evaluation visit 1.

This second treatment (either half-dose PDT or HSML treatment) will again be guided by the hyperfluorescent area(s) on the ICG angiography that correspond(s) to SRF accumulation in the macula on the OCT scan and the hyperfluorescent “hot spots” on the midphase (approximately 3 minutes) fluorescein angiogram.

In cases where there is no more SRF under the fovea but there is persistent fluid within the macular area encircled by the optic disc and temporal retinal vascular arcade, retreatment will be performed. The rationale behind this second treatment is that the persistent fluid may be interpreted as an incomplete treatment response because SRF accumulation indicates ongoing disease activity due to choroidal vascular hyperpermeability and fluid leakage through the RPE.

Note that if a patient did not require retreatment at evaluation visit 1 (=6-8 weeks after treatment visit 1) according to the protocol but returns with visual symptoms in the period between evaluation visit 1 and the follow-up visit at 7 to 8 months, a regular clinical examination should be performed that includes at least a measurement of visual acuity, ophthalmoscopy, and OCT scan to determine whether SRF has reoccurred. If there is evidence of recurrence of SRF on OCT (and therefore disease activity), these findings should be noted in the CRF. In these cases, additional evaluations compatible with evaluation visit 2 should be performed, and the patient should be planned for treatment visit 2 (max. 2 to 3 weeks after evaluation visit 2). Further evaluation will adhere to the retreatment criteria described above.

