#### Multivariate analysis

##### Analysis for the secondary endpoints

For the secondary endpoints, the following analyses will be performed:Anatomic results based on OCT scan (absence of SRF versus persistent SRF) at evaluation point 1 will be compared to the baseline.Number of subsequent treatments needed in each treatment arm.Mean change from baseline in ETDRS BCVA in the study eye at 6 to 8 weeks after treatment and at the end evaluation will be compared between the two treatment modalities.Mean change from evaluation point 1 in ETDRS BCVA in the study eye at final evaluation among those with subsequent and those without subsequent treatment will be compared between the two treatment modalitiesMean change from baseline in retinal sensitivity in the study eye to 6 to 8 weeks after treatment will be compared between the two treatment modalities.Mean change from baseline in the NEI-VFQ-25 questionnaire to 6 to 8 weeks after treatment will be compared among the two treatment modalities.

The first two analyses will be performed by the use of a cross-table. Furthermore, the continuous secondary variables will be analyzed using an ANCOVA model with baseline as and treatment as factor. For categorical secondary endpoints, a chi-square test will be performed. In addition, a logistic model with baseline as covariate and treatment as factor will be performed. The change from baseline in the NEI-VFQ-25 questionnaire results will be summarized descriptively.

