#### Number of participants

*Justification of sample size: total number of patients is 156*

For HSML, an anatomic success rate of approximately 50 %, defined as no SRF on OCT, after 6 to 8 weeks may be estimated based on retrospective studies [48, 56]. For half-dose PDT, approximately 80 % anatomic success may be estimated [18, 26–35]. Taking such a difference of 30 % in treatment success into account, a power calculation indicates that one would need 40 patients per treatment arm (power: 80 %, α: 0.05). However, when we also correct for factors such as positive publication bias and our own empiric treatment experience, we expect to find a difference in treatment success rate of approximately 22 % in favor of half-dose PDT. If we take one interim analysis into account, according to the O’Brien-Fleming method, 78 patients per treatment arm would be required (power: 80 %, α: 0.05).

*Distribution of subjects per site*

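### The only 7 to 8 month subretinal-fluid endpoint compares the arms among early responders, so randomisation does not protect it; add a comparison in all randomised eyes

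*Protocol article*

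**What the plan says.** **Late SRF.** Under Secondary endpoints, the protocol article lists "An absence of SRF on evaluation with OCT scanning as compared to HSML treatment at 7 to 8 months follow-up after successful treatment". A bracket in the same item defines success as a dry OCT 6 to 8 weeks after treatment. No other item there or under Analysis for the secondary endpoints concerns SRF at 7 to 8 months.

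**Expected early difference.** Under Number of participants, HSML is given "an anatomic success rate of approximately 50 %, defined as no SRF on OCT". After a correction for publication bias and the team's own experience, "we expect to find a difference in treatment success rate of approximately 22 % in favor of half-dose PDT".

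**Retreatment.** Under Retreatment criteria and considerations, "If there still is SRF present in the macular area, a second treatment will be performed". An eye that was dry at visit 1 but has a symptomatic, OCT-confirmed recurrence also goes on to retreatment: "the patient should be planned for treatment visit 2".

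**Late BCVA.** There are two analyses.
- Change from baseline to 7 to 8 months by arm, with no split. Both sections list it; the analysis section says that the change "at the end evaluation will be compared between the two treatment modalities".
- Change from evaluation visit 1 to the final visit. The endpoint section compares "among those who required one treatment and those who required a second treatment, and among the two treatment modalities overall". The analysis section keeps the split by subsequent treatment and does not repeat the overall part.

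**The concern.** Randomisation makes the two whole arms comparable ("Enrolled patients will be randomized at a 1:1 ratio"). It does not make the early responders of one arm comparable with those of the other once treatment affects who responds. If half-dose PDT clears more eyes, its responder group contains eyes that HSML would not have cleared. In the HSML arm the matching eyes sit among the non-responders and drop out of the comparison. If those extra eyes are harder to keep dry, PDT looks less durable because it worked in more patients.

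The endpoint is worded as a comparison with HSML, not as a summary within each arm, so a reader will take the difference as a treatment effect. Durability is the natural question after a 6 to 8 week primary result, and the protocol itself ties prolonged detachment to permanent visual loss. As listed, the endpoints do not include the fraction of all randomised eyes that is dry at the end.

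The BCVA analysis split by retreatment has a related weakness, because its strata depend on response.

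**Working it through.** **1. The plan's own figures.** With n = [1.96·√(2p̄(1−p̄)) + 0.842·√(p₁(1−p₁)+p₂(1−p₂))]² / (p₁−p₂)²:
- 50 v 80%: 39 per arm (stated 40).
- 50 v 72%: 76 per arm; times an O'Brien-Fleming inflation of about 1.008 for two looks, 77 (stated 78).
- 58 v 80%: 69 per arm, or 78 with continuity correction.

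The sample size reproduces. The protocol gives the 22-point difference without its base rate, so 50 v 72% and 58 v 80% serve below as an assumed range.

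**2. Who is compared.** Assume that no eye clears on HSML but not on PDT. With 78 per arm:

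| Base rates (HSML v PDT) | HSML responders | PDT responders | PDT responders that HSML would not clear |
|---|---|---|---|
| 50 v 72% | 0.50 × 78 = 39 | 0.72 × 78 ≈ 56 | 0.22/0.72 = 30.6% |
| 58 v 80% | 0.58 × 78 ≈ 45 | 0.80 × 78 ≈ 62 | 0.22/0.80 = 27.5% |

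**3. Effect on the late comparison.** The protocol gives no recurrence figures, so durability is assumed. Let 90% of the eyes that clear on either treatment stay dry in both arms, and let a fraction s of the extra PDT responders stay dry. At 50 v 72%:
- PDT among responders: (0.50 × 0.90 + 0.22·s)/0.72. HSML among responders: 0.90.
- PDT sustained clearance, whole arm: 0.50 × 0.90 + 0.22·s. HSML: 0.50 × 0.90 = 0.450.

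| s | Responders, PDT v HSML | Difference | Whole arms, PDT v HSML | Difference |
|---|---|---|---|---|
| 90% | 90.0 v 90.0% | 0 | 64.8 v 45.0% | +19.8 |
| 75% | 85.4 v 90.0% | −4.6 | 61.5 v 45.0% | +16.5 |
| 60% | 80.8 v 90.0% | −9.2 | 58.2 v 45.0% | +13.2 |
| 50% | 77.8 v 90.0% | −12.2 | 56.0 v 45.0% | +11.0 |

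At 58 v 80% and s = 60%, the responder difference is (0.58 × 0.90 + 0.22 × 0.60)/0.80 − 0.90 = −0.0825, and the whole-arm difference is again +13.2 points.

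**4. Sensitivity.** If PDT also raises durability to 95% in eyes that clear on either treatment (50 v 72%), the responder difference turns negative only when s falls below (0.90 × 0.72 − 0.50 × 0.95)/0.22 = 0.786. At s = 60% it is −5.7 points.

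**5. Strategy comparison.** Suppose further that 30% of first-treatment failures are dry after retreatment in both arms, and take s = 60%. Then PDT is 0.582 + 0.28 × 0.30 = 66.6% and HSML is 0.450 + 0.50 × 0.30 = 60.0%, a difference of +6.6 points. This answers a different question from sustained clearance, so both are worth stating.

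**6. BCVA split by retreatment.** Assumed letter changes (baseline to visit 1, then visit 1 to final) at 50 v 72%:
- Eyes that clear on either treatment: +5 then +1 in both arms.
- Eyes that clear only on PDT: +4 then 0 on PDT; 0 then +3 on HSML.
- Eyes that clear on neither: 0 then −1 in both arms.

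Change from visit 1, PDT v HSML:
- One treatment: (0.50 × 1 + 0.22 × 0)/0.72 = 0.69 v 1.0.
- Two treatments: −1.0 v (0.22 × 3 − 0.28 × 1)/0.50 = 0.76.

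PDT looks worse in both strata. Yet baseline to final by whole arm is 0.50 × 6 + 0.22 × 4 − 0.28 = 3.60 v 0.50 × 6 + 0.22 × 3 − 0.28 = 3.38, in favour of PDT.

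**The case against.** Whether treated eyes stay dry once they have cleared is a fair clinical question, and a responder summary answers it within each arm. The plan also has comparisons that are not limited to responders: the primary endpoint, the number of second treatments per arm, and functional outcomes at 7 to 8 months. The count of second treatments captures visit-1 failures and symptomatic recurrences, so it overlaps with sustained clearance. The analysis section names no analysis specific to the late SRF endpoint, and the full protocol or analysis plan may define its population further. All of this stands, and it narrows the gap. It does not close it: the endpoint is worded as a comparison with HSML, and the count of second treatments misses symptom-free recurrences first seen at the final visit.

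Three stronger readings are tempting, and the document does not support them.
- *The plan will show PDT as less durable.* This needs the extra PDT responders to recur more often. The document has no durability figures, and with equal durability the responder difference is zero.
- *Late BCVA is compared only within groups split by retreatment.* Change from baseline to the final visit by whole arm is planned in both sections, and continuous secondary variables are assigned to ANCOVA with baseline and treatment.
- *Retreatment status is the same variable as SRF at visit 1.* It is not, because an eye dry at visit 1 can be retreated for a later recurrence.

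**Conclusion.** The point holds for the late SRF endpoint. Its population is selected on the primary outcome, and no SRF comparison at 7 to 8 months in all randomised eyes is listed. With the trial's own 22-point difference, 28 to 31% of PDT responders would have no counterpart among HSML responders. Over the durability range shown, the responder comparison lies between 0 and 12.2 points against PDT, while sustained clearance in whole arms favours PDT by 11.0 to 19.8 points. Even at the mildest setting, the responder result hides a difference of about 20 points.

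These sizes rest on assumptions: the base rates, no eye clearing only on HSML, and the durability values. What does not depend on them is that randomisation does not protect the comparison.

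For BCVA, only the retreatment-split change from evaluation visit 1 is affected. This is a low-cost improvement to secondary endpoints.

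**What to change.** - Add as a secondary endpoint SRF absence at 7 to 8 months in all randomised eyes, by assigned arm, described as a comparison of strategies of up to two treatments of the same type.
- Add sustained clearance in all randomised eyes: dry at evaluation visit 1 and at the final visit, without a second treatment. This also settles how an eye counts if it recurs, is retreated and is dry at the end.
- Keep the responder-only result as a descriptive summary within each arm, with no test between arms.
- Leave the whole-arm BCVA change from baseline to 7 to 8 months as it is. In the analysis section, restore the overall comparison of change from evaluation visit 1 and label the split by retreatment descriptive. The overall comparison starts from a post-treatment value (in the illustration above it is 0.50 − 0.28 = 0.22 v 0.50 + 0.66 − 0.28 = 0.88 letters), so the change from baseline should stay the main late BCVA result.

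The cost is wording only. Summary of trial design already schedules OCT at the final visit, so no visit, scan or patient is added.
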